##### **Exclusion**

1. Patient with co morbid conditions like DM, HT, BA
2. Patients with severe primary respiratory disease or other pathogenic microbial pneumonia that needs to be identified with COVID-19
3. Pregnant and mothers, those who have a pregnancy plan.
4. Patients with other systemic malignant diseases such as malignant tumors, mental illnesses, etc., which the researchers consider unsuitable for participation in the study
5. People who have been allergic to Siddha medicine or intolerant to taking medicine
6. Patients participating in other COVID-19 clinical trials

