### Eligibility criteria {10}

#### Study participants

##### **Inclusion**

1. Laboratory confirmed COVID-19 without symptoms
2. Aged 18-55 years
3. Consenting to participate in the study and sign the informed consent

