### Specimen labelling and processing

Personal protective equipment (apron, hand gloves, face shield, N95 Masks etc.) will be used and all biosafety precautions will be followed so as to protect individuals and the environment. Proper labelling (name/age/gender/specimen ID) will be done on specimen container and other details of sender (name/address/phone number) on the outer container by mentioning “KSK\_COVID\_trial”

[figure not shown]

Figure 1: Lab Specimen collection

Laboratory sample collection Schedule: (i) Oropharyngeal swabs (0,7,14 days) - for SARS-CoV-2 RT-PCR (samples will be transported to Laboratory, as per the guidelines); (ii) Blood sample (0,7,14 days) (iii) ECG, Xray (Base line)

All samples would be stored for future-related tests.

Table 4: Schedule of investigations

| Parameter              | D0 | D7 | D14 |
|------------------------|----|----|-----|
| Haemogram\$            | ✓  | ✓  | ✓   |
| *LFT                   | ✓  |    | ✓   |
| #RFT                   | ✓  |    | ✓   |
| HbA1c, BS              | ✓  |    |     |
| qRT- PCR for SARS Cov2 | ✓  | ✓  | ✓   |
| Electrolytes           | ✓  | ✓  | ✓   |
| Chest X-ray            | ✓  |    |     |
| ECG                    | ✓  |    | ✓   |
| Immunoglobulins        | ✓  | ✓  | ✓   |

\$Hb%, total leucocyte count and differential WBC -neutrophils, lymphocytes, eosinophils, monocytes and basophils, RBC count, platelet count; #Renal function test -BUN, Creatinine; \*Liver function test -albumin, bilirubin, ALT, AST, alkaline phosphatase. AST, aspartate transaminase; ALT, alanine aminotransferase; RBC, red blood cell; WBC, white blood cell; BUN, blood urea nitrogen; ECG, electrocardiogram; SARS-CoV-2, severe acute respiratory syndrome coronavirus 2; qRT-PCR, real-time reverse transcription-polymerase chain reaction; HbA1c, haemoglobin A1c; Hb, haemoglobin

Frequency and duration of monitoring: (i) Patients will be monitored daily until discharge from the hospital and followed up till 14 days;

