### Data collection {19}

At the time of recruitment, we will collect socio-demographics, history of illness and clinical examination. At every visit we will do systematic clinical examination, determine adherence to interventions and assessment about any complaints and any adverse events. Both allopathic and Siddha physicians will perform clinical examination and collect relevant details according to their systems.

**Baseline laboratory investigations:** (i) Haemogram; (ii) Liver function tests (LFTs); (iii) Renal function tests (RFTs); (iv) Haemoglobin A1c and blood sugar, (v) RT-PCR for SARS-CoV-2 (respiratory samples: nasopharyngeal swab, oropharyngeal swab, in addition, sputum, bronchoalveolar lavage (BAL), if available); (vi) electrolytes, (vii) Chest X-ray; (viii) Electrocardiogram (ECG) (ix) Immunoglobulins

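### Exclusion 3 is over-broad and ambiguous about mothers, and neither legible test list includes a pregnancy test to support the exclusion of pregnancy

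*Protocol*

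**What the plan says.** The inclusion criteria set the age range ("Aged 18-55 years") and do not restrict by sex, so women of childbearing age can enrol. Exclusion 3 reads "Pregnant and mothers, those who have a pregnancy plan". No word qualifies mothers, and neither breastfeeding nor lactation is mentioned elsewhere in the protocol.

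Data collection {19} describes what is gathered at entry: "At the time of recruitment, we will collect socio-demographics, history of illness and clinical examination". It then lists nine baseline investigations: "i) Haemogram; (ii) Liver function tests (LFTs); (iii) Renal function tests (RFTs); (iv) Haemoglobin A1c and blood sugar", then "v) RT-PCR for SARS-CoV-2", then "vi) electrolytes, (vii) Chest X-ray; (viii) Electrocardiogram (ECG) (ix) Immunoglobulins". The table headed "Table 4: Schedule of investigations" covers the same ground in nine rows, all ticked at D0. Neither list has a pregnancy test.

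The section on specimen labelling and processing schedules a blood sample on days 0, 7 and 14 and a chest X-ray at baseline. The intervention section sets a 14-day course of a 15-ingredient decoction in the KSK arm. Allocation is by numbered envelopes opened as each patient is enrolled.

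**The concern.** There are two related defects.

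The first is wording. An eligibility rule should give the same answer whoever applies it. Under the literal reading, a 50-year-old woman with adult children is excluded. Under the likely intended reading, she is not. The protocol does not say which applies, and its data collection section has physicians of two systems of medicine examining patients, so more than one person may have to interpret the rule.

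The second is ascertainment. The protocol decided that pregnancy excludes a patient, but the screening that can be read in it has no means of finding a pregnancy that the woman does not know about. Such a woman could have the baseline chest X-ray and, if allocated to KSK, the 14-day course. The Rationale cites a toxicological study of KSK but describes no reproductive safety data, so nothing in the text makes the exclusion a formality.

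**Working it through.** No formula applies, and the plan states no figure to reproduce. The check sets the eligibility wording beside the listed procedures.

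**Step 1: whom Exclusion 3 covers, under each reading**

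| Woman | Literal reading (any mother) | Likely intended reading (breastfeeding mothers) |
|---|---|---|
| Pregnant, known | excluded | excluded |
| Pregnant, unrecognised | excluded by the rule | excluded by the rule |
| Breastfeeding | excluded, as a mother | excluded |
| Has children, not pregnant, not breastfeeding, no pregnancy plan | excluded | not excluded |
| Planning a pregnancy | excluded | excluded |

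The two readings differ in one row only. The ambiguity therefore concerns women who have children and would otherwise be eligible.

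**Step 2: whether the listed screening can apply the pregnancy part**

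- Baseline list under Data collection {19}: haemogram, liver function, renal function, HbA1c and blood sugar, RT-PCR, electrolytes, chest X-ray, ECG, immunoglobulins. Pregnancy tests: 0 of 9.
- Table 4: the same nine items as rows. Pregnancy tests: 0 of 9 at D0, and none at D7 or D14.
- Other information at recruitment: socio-demographics, history and clinical examination. These can identify a known or advanced pregnancy but cannot exclude an early, unrecognised one.

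Diabetes under Exclusion 1 makes a useful contrast: there the baseline list does contain a relevant measurement, "Haemoglobin A1c and blood sugar".

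**Step 3: who could be exposed**

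With 30 patients planned per arm, a woman enrolled with an undetected pregnancy would be allocated to KSK with probability 30/60 = 1/2. The baseline chest X-ray applies to both arms. How many such women there might be cannot be derived, because the protocol gives no figures on sex, parity or pregnancy.

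**Step 4: limits of the evidence**

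The intervention section contains an assessment schedule of which part is illegible in the public copy; only its last two rows survive. A pregnancy test in the lost part cannot be fully ruled out. If one exists there, Table 4 and the baseline list disagree with it and would still need to be brought into line.

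**The case against.** The strongest reply is that this is a slip of grammar and no more. The phrase looks as if a word before mothers was dropped, in drafting or when the text was extracted, although no gap or redaction mark shows it. The trial runs at a single centre, so sites cannot differ. The criterion acts before allocation and applies equally to both arms, so it cannot bias the comparison of KSK with CZ. All of that is fair, and it limits the point to safety and clarity. It does not answer the missing pregnancy test, which stands whatever the missing word was.

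Some stronger inferences are tempting, and the documents do not support them:

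- *Breastfeeding women can be enrolled because they are not named.* They are mothers, so they are barred under either reading.
- *A woman with an unrecognised pregnancy meets every criterion.* She does not; Exclusion 3 bars her. The gap is that the listed screening cannot detect her.
- *Pregnancy status rests on self-report alone.* The protocol also provides for history and clinical examination. It does not say how pregnancy status is established.
- *The sample will be mostly male or childless.* That requires staff to apply the literal reading, together with figures on sex and parity that the protocol does not give. A 60-patient pilot that already excludes comorbid patients also makes no claim to represent all asymptomatic adults in this age range.

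**Conclusion.** The point holds as a specific gap in eligibility wording and safety screening. Exclusion 3 is broader than its likely purpose and leaves its meaning to whoever applies it. The procedures that can be read in the protocol cannot detect an early, unrecognised pregnancy, although the protocol means to exclude it.

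Its size can be stated only in terms of text: no pregnancy test among nine items in either of the two complete lists, and no mention of breastfeeding or lactation. The number of women turned away or exposed is unknown.

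The conclusion assumes that the illegible part of the schedule contains no pregnancy test, and that the wording of Exclusion 3 in the public copy is complete. If the second assumption fails, the wording point weakens and the pregnancy-test point is untouched. The comparison between arms, the sample size and the analysis are unaffected. The change is worth making because it protects participants at little cost, but the gap does not undermine the trial.

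**What to change.** 1. Have the sponsor reword Exclusion 3 so that it states whom mothers means. One example, if it matches the intent, is women who are pregnant, breastfeeding or planning pregnancy.
2. Add a pregnancy check at D0 for women of childbearing potential to both Table 4 and the baseline list under Data collection {19}. It could be run on the D0 blood already drawn.
3. State that the result must be known before the allocation envelope is opened, and where the check falls relative to the baseline chest X-ray.
4. If the illegible schedule already contains such a test, align the other two lists with it.

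The cost is one reworded line, an inexpensive test in the women of childbearing potential among about 60 patients, and a short wait before allocation. No change to the sample size or the analysis is needed.

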### Interventions Arm -1{11a}

#### **Kabasura Kudineer (Siddha Polyherbal decoction)**

Table 1: Composition of KSK

| S. No | Botanical name                 | Family         | Part Used   | Parts  |
|-------|--------------------------------|----------------|-------------|--------|
| 1.    | Zingiber officinale     | Zingiberaceae  | Rhizome     | 1 part |
| 2.    | Piper longum            | Piperaceae     | Fruit       | 1 part |
| 3.    | Syzygium aromaticum     | Myrtaceae      | Flower bud  | 1 part |
| 4.    | Anacyclus pyrethrum     | Asteraceae     | Rhizome     | 1 part |
| 5.    | Tragia involucrata      | Euphorbiaceae  | Leaves      | 1 part |
| 6.    | Solanum anguivi         | Solanaceae     | Leaves      | 1 part |
| 7.    | Terminalia chebula      | Combretaceae   | Fruit rind  | 1 part |
| 8.    | Justicia adathoda       | Acanthaceae    | Leaves      | 1 part |
| 9.    | Anisochilus carnosus    | Lamiaceae      | Whole plant | 1 part |
| 10.   | Costus speciosus        | Costaceae      | Rhizome     | 1 part |
| 11.   | Tinospora cordifolia    | Menispermaceae | Whole plant | 1 part |
| 12.   | Clerodendrum serratum   | Verbanaceae    | Leaves      | 1 part |
| 13.   | Andrographis paniculata | Acanthaceae    | Whole plant | 1 part |
| 14.   | Cyperus rotundus        | Cyperaceae     | Rhizome     | 1 part |
| 15.   | Sida acuta              | Malvaceae      | Whole plant | 1 part |

**SOP for preparation:** To 5g of KSK coarse powder, add 240 ml of water and allowed to boil till, it reduces to one-fourth (60ml) and filter the decoction (KSK).

**Dose** : 30 – 60 ml twice daily.  
**Dosage form** : Kudineer (decoction).  
**Route of administration** : Oral.  
**Time of administration** : twice a day- Morning and Night before food  
**Duration of therapy** : 14 days  
**Follow up period** : 14 days after treatment

[illegible]

|                    |  |   |   |   |   |   |   |   |   |   |   |   |   |   |   |   |
|--------------------|--|---|---|---|---|---|---|---|---|---|---|---|---|---|---|---|
| SSM principles     |  | ✓ | ✓ | ✓ | ✓ | ✓ | ✓ | ✓ | ✓ | ✓ | ✓ | ✓ | ✓ | ✓ | ✓ | ✓ |
| Laboratory Markers |  | ✓ |   |   |   |   |   | ✓ |   |   |   |   |   |   |   | ✓ |

### Sample size {14}

As there is no prior work on this research question, so no assumptions for the sample size calculation could be made. The present study will serve as a pilot trial. We intend to study 60 patients, each 30 in two groups.

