## Rationale: {6b}

In this context, one of the classical formulations from Siddha system of medicine is *Kabasura kudineer* (KSK) consists of 15 herbals ingredients which individually has anti-viral activity (6). Cucurbitacin B (-112.09), Cardiolipide (-111.5), Apigenin (-98.84) and Pyrethrin (-92.98) presented in the KSK were found to be effective in preventing novel corona virus binding and replication.(7) Determination of organoleptic characters, preliminary phytochemical analysis, physico- chemical analysis, TLC photo documentation and HPTLC fingerprint studies on KSK were analyzed.(8) Toxicological study on KSK showed that it is safe(9). KSK also possess anti pyretic, anti-inflammatory and anti-bacterial effect. Vitamin c and zinc supplementation(CZ) is being prescribed for the COVID19 positive asymptomatic patients admitted in isolation ward. The role of CZ in the management of COVID19 is still not clear. Therefore, we propose to compare the effect of KSK and CZ in terms of negative conversion of SARS CoV- 2 infection.

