## Objectives

### Primary:{7a}

- To determine efficacy of KSK compared with CZ in reducing the onset of clinical symptoms in asymptomatic patients
- To determine effectiveness of KSK compared with CZ in terms of reduction of SARS-CoV-2 viral load from the baseline
- To examine the effect of KSK compared with CZ on immune system in terms of selected immunological markers

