### Randomization, sequence allocation & allocation concealment{16a,b,c}

Simple randomization. All the eligible participants will be randomly assigned (in 1:1 ratio) in each arm to ensure balanced distribution between KSK and CZ arms. Randomization will be implemented by independent statistician who will not involve in data analysis. Equal numbers of cards with each arm assignment number randomly generated by computer will be placed in sequentially numbered envelopes that will be opened on patient enrolling.

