### Data Analysis plan {20}

The analysis plan on the primary and secondary outcome is described in the below table

Table 5: Statistical analysis plan{20a}

| Outcome                                                              | Hypothesis                                 | Outcome measure                                        | Methods of analysis            |
|----------------------------------------------------------------------|--------------------------------------------|--------------------------------------------------------|--------------------------------|
| Primary                                                       |                                            |                                                        |                                |
| Viral load of SARS-CoV-2                                             | Reduction of Viral Load after intervention | Viral Load                                             | T test                         |
| Immunological markers                                                | Improvement                                | Th1, Th2 cells                                         | T test                         |
| Secondary                                                     |                                            |                                                        |                                |
| Reduction in the risk of disease progression                         | Reduction of complication                  | Incidence of complication                              | Kaplan Meier survival analysis |
| Reduction in intensive supportive care and long-term hospitalization | Reduction of complication                  | Incidence of complication                              | Kaplan Meier survival analysis |
| Clinical profile in terms of Siddha System of Medicine (SSM)         |                                            | Questionnaire                                          | Chi-square test                |
| Adverse events/effects                                               |                                            | Presence of drug related adverse event (time to event) | Kaplan Meier survival analysis |

**Data monitoring {21a}:** The data safety monitoring committee constituted by Ministry of AYUSH will be responsible for the monitoring the data

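### A declared pilot of 30 per arm, sized without assumptions, sets three unranked comparative primary objectives, and the protocol does not agree with itself on what is primary

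*Protocol*

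**What the plan says.** Four places in the Protocol bear on this.

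- **Sample size {14}.** "As there is no prior work on this research question, so no assumptions for the sample size calculation could be made". The section then says "The present study will serve as a pilot trial" and "We intend to study 60 patients, each 30 in two groups".
- **Objectives, Primary {7a}.** There are three objectives, all comparing KSK with CZ and none ranked above another. The first is "To determine efficacy of KSK compared with CZ in reducing the onset of clinical symptoms in asymptomatic patients". The second uses the same verb with effectiveness in place of efficacy, for viral load reduction from baseline. The third is to examine the effect on selected immunological markers. None is a feasibility or estimation aim.
- **Data Analysis plan {20}, Table 5.** Two primary outcomes are listed: viral load, and "Immunological markers" measured by Th1 and Th2 cells. Each is given a t test. Neither is ranked, and symptom onset has no row.
- **Rationale {6b}.** The proposed comparison is stated in terms of negative conversion. Time to a negative test appears again under Outcome assessment, but not as a primary outcome in Table 5.

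**The concern.** The label and the aims do not fit together. A study sized without assumptions can estimate a difference and show how precisely it was estimated. It has not been designed to settle whether KSK is efficacious, which is what the first two objectives promise.

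The sections also disagree on what the trial is mainly about. The objectives give three primary questions, Table 5 gives two primary outcomes, and the Rationale gives a fourth quantity. The only objective worded as efficacy is the one Table 5 does not analyse.

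Two things are at stake. If the text is followed as written, several primary tests are run with none singled out, so a nominally significant result on any of them could be taken as the trial's positive finding. And a claim worded as determining efficacy would rest on a sample whose precision is nowhere stated.

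**Working it through.** **1. The plan's own figure.** The 60 patients cannot be reproduced by calculation. No significance level, power, effect size, SD or event rate is given, and the section says so openly.

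**2. What each section treats as primary.**

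| Quantity | Primary objective {7a} | Primary row in Table 5 | Stated aim in Rationale {6b} |
|---|---|---|---|
| Symptom onset | Yes (efficacy) | No row | No |
| Viral load | Yes (effectiveness) | Yes, t test | No |
| Immune markers | Yes (examine) | Yes, Th1 and Th2, t test | No |
| Negative conversion | No | No row | Yes |

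No quantity is primary in all three places.

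**3. False-positive chance.** Inputs: two tests if each Table 5 primary row counts once; three if Th1 and Th2 are tested separately beside viral load. Assumption: two-sided 5% per test, unadjusted. For k independent tests the chance of at least one false positive is 1 − 0.95^k.

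- k = 2: 1 − 0.9025 = 0.0975, about 10%.
- k = 3: 1 − 0.8574 = 0.1426, about 14%.

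Outcomes in the same patients are likely to be correlated, which lowers these figures. Simulation of equally correlated normal test statistics (400,000 draws) gave:

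| Correlation | Two tests | Three tests |
|---|---|---|
| 0.5 | 9.1% | 12.5% |
| 0.9 | 7.1% | 8.3% |

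Every case stays above 5%.

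**4. What 30 per arm can show.** Inputs: 30 per arm (Sample size {14}) and 1:1 allocation (Randomization {16a,b,c}), all patients evaluable. The t test is read as a two-sample comparison between arms, since the objectives are comparisons. Two-sided 5% and 80% power are assumed.

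- Half-width of the 95% confidence interval for a difference in means, in SD units: t(0.975, 58) × √(2/30) = 2.002 × 0.2582 = 0.517, about 0.52 SD.
- Difference detectable with 80% power on one endpoint, normal approximation: (1.960 + 0.842) × 0.2582 = 0.723 SD. The exact t-test calculation gives 0.736, about 0.74 SD.
- Power for a true difference of 0.5 SD, exact t test: 0.478, about 48%.
- If three primaries were kept with a Bonferroni split (0.05/3 each), the detectable difference rises to 0.857, about 0.86 SD.

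**The case against.** The sample size section is candid. It admits that no assumptions could be made and calls the study a pilot, which is disclosure and not an error. A significance level and a multiplicity rule are commonly left to a statistical analysis plan, and one may exist that is not shown. Both points stand. They do not remove the mismatch: which objectives and outcomes are primary is a protocol decision, and this protocol prints its own analysis table that disagrees with its objectives.

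Several stronger readings are tempting and are not supported.

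- **A much higher false-positive rate.** A reader might count viral load, Th1 and Th2 at both day 7 and day 14 (1 − 0.95^6 = 26.5%), or add symptom onset (1 − 0.95^7 = 30.2%). Table 5 does not call for testing at both days, and its viral load hypothesis refers to the period after intervention. Table 4 schedules immunoglobulins, not Th1 and Th2, on those days. Symptom onset has no row to test.
- **No time point anywhere.** The available text is illegible between items {11a} and {14}, so it is unsafe to say that the protocol never fixes one.
- **The missing sample-size basis inflates false positives.** It leaves power unaddressed but does not raise type I error. Any inflation comes from the unranked primary tests.
- **A null result would be presented as KSK being as good as CZ.** The Rationale does say "The role of CZ in the management of COVID19 is still not clear", but no equivalence or non-inferiority claim appears anywhere in the document.
- **No support at all for an efficacy claim.** This is too absolute. On one prespecified endpoint, 30 per arm has 80% power for about 0.74 SD, and an estimate with its interval informs the KSK versus CZ question at any size.

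**Conclusion.** The point holds as an internal inconsistency with a modest, conditional statistical cost. The declared pilot status does not match two objectives worded as determining efficacy and effectiveness, and the Rationale, objectives and Table 5 give three different accounts of what is primary. Table 5 as printed implies two or three unranked primary tests. At an assumed two-sided 5% each, the chance of at least one false positive is about 10% to 14% if they are independent; for three tests it is about 12.5% at correlation 0.5 and 8% at 0.9.

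The precision of 30 per arm, about 0.52 SD either side of the estimate, suits estimation in a pilot. What the design lacks is error-controlled, confirmatory support for an efficacy claim, unless one endpoint is singled out and the difference is large. These figures assume 30 evaluable patients per arm and a between-arm t test; an unseen analysis plan could lower the false-positive figures but could not reconcile the protocol's own sections.

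**What to change.** Change wording in four sections so that they agree.

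1. **Objectives {7a} and Table 5:** name one primary endpoint at one time point. One example is the between-arm difference in change from baseline in log10 viral load, at a time the sponsor fixes in advance. The choice is the sponsor's, provided there is only one.
2. **Same sections:** make the other outcomes, including symptom onset and Th1/Th2, secondary. Report them with 95% confidence intervals and no confirmatory claim, and give symptom onset a row in Table 5.
3. **Objectives {7a}:** replace the determine-efficacy and determine-effectiveness wording with *To estimate, in a pilot, the difference between KSK and CZ*, followed by the outcome.
4. **Sample size {14}:** add that 30 per arm gives a 95% confidence interval half-width of about 0.52 SD for a difference in means.
5. **Rationale {6b}:** bring the negative-conversion aim into line with the chosen primary endpoint, or state its secondary place.

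The cost is a protocol wording change, with no more patients, visits or samples. The downside is a more modest stated claim, and two of the three objectives lose primary status.
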